#### **1.5.3.2 Efficacy trial**

The sample size is calculated based on the primary objectives only. A minimum of 750 SAM children below 24 months of age and 450 SAM children 24 to 59 months of age is required to be 80% sure that the upper limit of a one-sided 95% confidence interval will exclude a difference in recovery rate in favour of the standard group of more than 10%. In addition 60 community control children will be enrolled for the Deuterium dilution technique sub-study. The number of children to be enrolled as community control of children discharged alive and for whom the follow up is possible will depend on the number of children meeting follow up eligibility criteria.

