## 2.5.3 Sample size and randomisation

### 2.5.3.1 Sample size

For the acceptability trial, a convenience sample of 20 children per group will be used. For assessing efficacy, the different sample sizes are calculated for a power of 80% and a level of significance of 0.05. The total sample size will be the total of sample required for the SO1 and SO2. For the other SOs, the calculated sample was lower than that required for the total sample for SO1 and SO2 as indicated in table 2 below.

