**Table 2: Sample size according to the specific objective for the efficacy study**

| Specific objective | endpoint                                           | Research design                   | Assumptions                                                                                                      | Calculated sample                               |
|--------------------|----------------------------------------------------|-----------------------------------|------------------------------------------------------------------------------------------------------------------|-------------------------------------------------|
| SO1                | Recovery rate
6-23 months                       | Non-inferiority
clinical trial | Recovery rate
P-RUTF, FSMS-RUTF, MSMS-
RUTF= 75.5%
Non-inferiority margin=10%
Loss to follow up =10% | 250 per arm.
Total=750 SAM children          |
| SO2                | Recovery rate
24-59 months                      | Non-inferiority
clinical trial | Recovery rate P-RUTF, FSMS-RUTF,
MSMS-RUTF = 88.2%
Non-inferiority margin=10%
Loss to follow up =10%    | 150 per arm.
Total=450 SAM children          |
| SO3                | Mean
weight gain
6-23 months                 | Non-inferiority
clinical trial | Standard deviation=4.1
non-inferiority margin =1.5g/kg/d
Loss to follow up=10%                             | 110 children/arm
Total=330 SAM children      |
| SO4                | Mean
weight gain
24-59 months                | Non-inferiority
clinical trial | Standard deviation=3.5
non-inferiority margin =1.5g/kg/d
Loss to follow-up=5%                              | 75 children/arm
Total=225 children           |
| SO5                | Mean
Length of stay
6-23 months              | Non-inferiority
clinical trial | Standard deviation=22.8
non-inferiority margin = 14 days
Loss to follow up=10%                             | 40 children/arm
Total= 120 children          |
| SO6                | Mean
Length of stay
24-59 months             | Non-inferiority
clinical trial | Standard deviation=9.9
non-inferiority margin = 14 days
Loss to follow up=10%                              | 30 children/arm
Total= 90 children           |

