### 2.5.6.2 Efficacy trial

#### 2.5.6.2.1 Statistical analysis strategy

Data will be analysed by a statistician blinded as to type of food of the different group allocation. Both the intention-to-treat (ITT) and Per Protocol (PP) analyses will be used for data analyses. However, as per the recommendation of the CONSORT group, in case of opposition between conclusions from the ITT and PP analyses, the final conclusion will be based on PP analyses as ITT analyses inflate type-I error.

Appropriate quantitative methods will be used to provide answers to the study questions. As recommended by Piaggio et al. of the CONSORT (Consolidated Standards of Reporting Trials) group, the assessment of non-inferiority, the confidence interval approach will be used for the interpretation [98]. The figure 1 below illustrates the interpretation.

**Figure.** Possible Scenarios of Observed Treatment Differences for Adverse Outcomes (Harms) In Noninferiority Trials

[figure not shown]

Error bars indicate 2-sided 95% confidence intervals (CIs). Tinted area indicates zone of inferiority. A, If the CI lies wholly to the left of zero, the new treatment is superior. B and C, If the CI lies to the left of  $\Delta$  and includes zero, the new treatment is noninferior but not shown to be superior. D, If the CI lies wholly to the left of  $\Delta$  and wholly to the right of zero, the new treatment is noninferior in the sense already defined, but it is also inferior in the sense that a null treatment difference is excluded. This puzzling case is rare, since it requires a very large sample size. It can also result from having too wide a noninferiority margin. E and F, If the CI includes  $\Delta$  and zero, the difference is nonsignificant but the result regarding noninferiority is inconclusive. G, If the CI includes  $\Delta$  and is wholly to the right of zero, the difference is statistically significant but the result is inconclusive regarding possible inferiority of magnitude  $\Delta$  or worse. H, If the CI is wholly above  $\Delta$ , the new treatment is inferior.

\*This CI indicates noninferiority in the sense that it does not include  $\Delta$ , but the new treatment is significantly worse than the standard. Such a result is unlikely because it would require a very large sample size.

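### The primary comparisons are sized on a one-sided 95% limit, but the analysis section reads non-inferiority from two-sided 95% intervals, and nothing reconciles the two

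*Protocol*

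**What the plan says.** Three places in the protocol bear on the decision rule for the primary endpoint.

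- Section 1.5.3.2 (summary, sample size for the efficacy trial) says the planned number of children "is required to be 80% sure that the upper limit of a one-sided 95% confidence interval will exclude a difference" of more than 10 percentage points in recovery. That is a one-sided alpha of 0.05.
- Section 2.5.3.1 says that "the different sample sizes are calculated for a power of 80% and a level of significance of 0.05". It does not say whether the level is one-sided or two-sided. Table 2 gives "250 per arm. Total=750 SAM children" for ages 6-23 months, and 150 per arm (450 in total) for ages 24-59 months.
- Section 2.5.6.2.1 says that for non-inferiority "the confidence interval approach will be used for the interpretation", and then that "The figure 1 below illustrates the interpretation". The legend of that figure reads "Error bars indicate 2-sided 95% confidence intervals (CIs", and it sorts results into non-inferior, inconclusive and inferior by where those bars lie relative to zero and the margin.

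The analysis section mentions no other interval, whether a two-sided 90% interval or a one-sided 95% limit.

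**The concern.** A two-sided 95% interval that must clear the margin is a one-sided test at 0.025. A one-sided 95% limit is a test at 0.05. The sample-size text uses the second and the interpretation text shows the first, so the protocol carries two thresholds for its primary conclusion.

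Two things are at stake. First, one set of results could be called non-inferior under section 1.5.3.2 and inconclusive under section 2.5.6.2.1, and the choice would be open after the data are seen. Second, the stated 80% power belongs to only one of the two rules.

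**Working it through.** **Inputs.** From Table 2: recovery 75.5% in all arms at 6-23 months and 88.2% in all arms at 24-59 months, margin 10 points, loss 10%, and 250 and 150 per arm. From section 2.5.3.1: power 80%.

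**Formula.** The protocol's own, given below Table 2. With equal true rates p and margin d = 0.10, it is n = f × 2p(1−p) / d², where f = (z for alpha + z for power)².

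- 2p(1−p) = 2 × 0.755 × 0.245 = 0.36995 for the younger group.
- 2p(1−p) = 2 × 0.882 × 0.118 = 0.20815 for the older group.
- f = (1.645 + 0.842)² = 6.183 at one-sided 0.05.
- f = (1.960 + 0.842)² = 7.849 at one-sided 0.025.

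**Step 1: reproduce the plan's sample sizes.** Enrolled is the evaluable number, rounded up, divided by 0.9.

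| | Evaluable per arm | Enrolled per arm | Stated |
|---|---|---|---|
| 6-23 months, one-sided 0.05 | 228.7 → 229 | 255 | 250 |
| 6-23 months, one-sided 0.025 | 290.4 → 291 | 324 | 250 |
| 24-59 months, one-sided 0.05 | 128.7 → 129 | 144 | 150 |
| 24-59 months, one-sided 0.025 | 163.4 → 164 | 183 | 150 |

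The stated sizes fit one-sided 0.05. The first is slightly below the formula value and the second slightly above it. Neither is near the 0.025 value.

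**Step 2: power under each rule.** Power = Φ(0.10 / SE − z), with SE = √(2p(1−p)/n).

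After 10% loss, n is 225 and 135:

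- 6-23 months: SE = √(0.36995/225) = 0.0405, and 0.10/SE = 2.466. At one-sided 0.05, Φ(0.821) = 79.4%. At two-sided 95%, Φ(0.506) = 69.4%.
- 24-59 months: SE = √(0.20815/135) = 0.0393, and 0.10/SE = 2.547. At one-sided 0.05, Φ(0.902) = 81.6%. At two-sided 95%, Φ(0.587) = 72.1%.

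With no loss, n is 250 and 150:

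- 6-23 months: 83.0% at one-sided 0.05, 73.9% at two-sided 95%.
- 24-59 months: 85.1% at one-sided 0.05, 76.6% at two-sided 95%.

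A simulation with Wald intervals at 225 and 135 per arm under the two-sided 95% rule gave 69.6% and 72.5%, in line with the formula.

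**Step 3: results on which the rules disagree.** Non-inferiority is shown when the observed deficit is below 10 points − z × SE. With the planning SEs after loss:

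- 6-23 months: below 10 − 1.645 × 4.05 = 3.3 points under the one-sided 95% limit, and below 10 − 1.960 × 4.05 = 2.1 points under the two-sided 95% interval.
- 24-59 months: below 10 − 1.645 × 3.93 = 3.5 points, and below 10 − 1.960 × 3.93 = 2.3 points.

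An observed deficit of about 2.1 to 3.3 points in the younger group, or 2.3 to 3.5 in the older, passes under one section and is inconclusive under the other.

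**The case against.** The strongest reply is that the two-sided wording sits in a borrowed legend. The figure is credited to a published reporting guideline, its title refers to adverse outcomes while recovery is a benefit, and it keeps reference superscripts that are not this protocol's. The authors' own sentence says only that the figure illustrates interpretation. The one trial-specific statement of an interval level is in section 1.5.3.2, and the primary sample sizes agree with it. On that reading the one-sided 95% limit governs, the legend was simply not adapted, and no power is lost.

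Much of this stands. A reader might infer that the trial is in fact powered at 69% and 72%. The documents do not settle that, because those figures hold only if the two-sided rule is the one applied. The reply does not remove the conflict, however. Section 2.5.6.2.1 adopts the figure as its scheme, and the legend is the only interval level the analysis section gives.

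A second reply is that an analysis plan, not seen here, may fix the level. It may, but the protocol states two levels rather than leaving the matter open, so either choice would depart from one section of it.

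A third reply is that the loss-adjusted figures are the low end. Recovery is defined over all exits, and an intention-to-treat analysis is also planned, so if every enrolled child counts, power under the two-sided rule is 74% and 77%. That is fair and the range should be shown. Both values remain below 80%, and section 2.5.6.2.1 lets the per-protocol analysis decide when the two analyses disagree.

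Two further inferences would go too far. One is that all of Table 2 reproduces only at one-sided 0.05. It does not: length of stay at 24-59 months (about 7 or 9 per arm against 30 stated) and height gain at 6-23 months (about 27 or 34 against 180) fit neither level. The other is that the legend inflates type I error. It does not, because the two-sided 95% rule is the stricter of the two.

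**Conclusion.** The point holds as an inconsistency between sections, not as an arithmetic error in the primary sample sizes, which are sound for a one-sided 0.05 level.

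If the two-sided 95% interval is the rule, power per pairwise comparison falls short of the stated 80% by about 6 to 11 points at 6-23 months (69% to 74%) and about 3 to 8 points at 24-59 months (72% to 77%). If the one-sided 95% limit is the rule, power after loss is about 79% and 82% and there is no material shortfall.

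These figures assume the recovery rates in Table 2, no true difference between arms, a 10-point margin, loss between none and the planned 10%, and one comparison at a time. They do not address the requirement that FSMS-RUTF be non-inferior to both other foods.

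**What to change.** Before the statistician is unblinded, name one interval and use it in sections 1.5.3.2, 2.5.3.1 and 2.5.6.2.1. Either:

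- state that non-inferiority is judged on the one-sided 95% limit (equivalently the two-sided 90% interval), add the word one-sided to the significance level in section 2.5.3.1, and say that the 95% bars in Figure 1 do not apply; or
- keep the two-sided 95% interval, correct section 1.5.3.2 to match, and restate the power per pairwise comparison as about 69-74% at 6-23 months and 72-77% at 24-59 months.

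Both are wording changes. The first leaves sample size and power as they are. The second costs a less favourable stated power. Keeping 80% under the two-sided rule would instead need about 324 and 183 children per arm (972 and 549 in total, against 750 and 450), which is 222 + 99 = 321 more children.

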## **2.6 Ethical considerations**

The study will be conducted in compliance with the Declaration of Helsinki. Permission for the trial to be conducted will be obtained from the Malawi National Health Sciences Research Committee and the Ajinomoto institutional review board. Participation will be voluntary. At the time of admission, each child's parent or carer will be informed about the nature and purpose of the study and asked for their verbal and written consent for their child to be included in the study and for their medical information to be used for research purposes. The caregivers will be informed that participation is voluntary and this information will be emphasised again on the information sheet. The carer information sheet and the consent form will be in English but will also be translated in Chichewa, the national language. The sheet will contain information on the study objectives, study procedures, anticipated duration of participation, potential risks and discomfort for the child, benefits for the child and for the under five population in general, conditions of study termination or participant withdrawal, confidentiality of records and contact persons if any question or problem arise. When parents or carer withhold consent for participation, children will be referred to non participating clinics providing care for SAM children. There are several such clinics in the selected Districts. They use standard P-RUTF. Any child who will develop study food related side effects or any serious disease during the study will be referred to the appropriate level of care and the cost of the treatment met by the research project.

Children participating in the acceptability trial will all receive Vitamin A and deworming drug. Any common illness that occurs during the study will also be treated and any cost not covered by the Government of Malawi scheme will be met by the research programme. Children with SAM admitted to the efficacy trial will benefit from the study interventions. When treated inappropriately SAM is associated with case fatality rates ranging from 20% to 30%. There is good evidence of the benefit of RUTF in reducing case-fatalities among children suffering from SAM, with its use in CMAM programmes reducing SAM-associated mortality from 20-30% to below 5% while increasing programme coverage from below 10% to around 50%. Thus, participating children will have an increased chance of survival and the results may contribute to the overall millennium development objectives of reducing under five mortality. Other benefits for participating children will include free medical care and nutrition and health counselling during the follow up. Children enrolled will receive free appropriate clinical care for all diseases including those not related to the intervention. Children diagnosed with HIV will be linked to the nearest governmental health facility providing specialised care for this disease and the transport costs for travelling to the health facility for specialised follow up will be covered throughout the study period. The benefit for community controls will include Vitamin A supplementation and deworming when needed, free treatment of illness identified during the assessment for inclusion and data collection including anaemia treatment, satisfaction of contributing to identifying solutions for addressing acute malnutrition in Malawi and the world as it has been for the CMAM and a soap as contribution to improving water sanitation and hygiene practices. Transport compensation will be given to the caregivers for each trip to participate to the activity.

## **2.7 Independent Data Monitoring Committee**

A committee of experts will be appointed to serve as an independent data monitoring and safety committee (DMC). The committee will include one academic, a representative of Ministry of Health who are not part of the research team, a member of the National Health Sciences Research Committee and a statistician not part of the research team. The committee will be appointed by the research team and the sponsor with approval from

the Nutrition Unit of the Ministry of Health. DMC will be chaired by the representative of the National Health Sciences Research Committee. The DMC will be notified monthly of the trial's progress and all the cases of study related side effects will be reported to the DMC as they are diagnosed. The DMC will meet at the beginning of the study and twice during the course of the study. However, the chairman of the committee will have the power to call for an extraordinary meeting in case of any report that is considered alarming including occurrence of a serious event due to study food. Indeed, any side effects judged serious will be immediately reported by phone and email to the DHO of the district, the chairman of the DMC and the principal investigators. The principal investigator will report on DMC meetings and decision to Ajinomoto and Valid Nutrition. The chairman of the DMC will have the right to decide an early discontinuation based on the committee risk/benefit assessment.

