#### **1.5.4.2 Efficacy trial**

Appropriate quantitative analysis will be used including descriptive statistics (proportion, percentage, mean or median), comparison of difference in proportion for binary outcome and comparison of average (mean or median as appropriate) change for continuous variable. Both intention to treat (ITT) and per protocol (PP) approaches will be used for data analysis and reporting. Data of children below 24 months and that of those aged 24 months or more will be analysed separately except for body composition and haemoglobin. Subgroup analyses assessing the effect of the intervention in different subgroups will be carried out. The variables considered for the sub-group analyses include gender, type of malnutrition (oedematous and non-oedematous) stunting and HIV status (positive or negative). Interactions between the interventions and other variables will be checked and data analysis scheme adjusted accordingly in case of a statistically significant interaction. No interim analysis will be performed except if the monitoring and safety committee identify need for such analysis.

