## **1.7 Ethical consideration:**

The study will be conducted in compliance with the Declaration of Helsinki. Permission for the trial to be conducted will be obtained from the National Health Sciences Research Committee and the Ajinomoto institutional review board. Participation will be voluntary. At the time of admission, each child's parent or carer will be informed about the nature and purpose of the study and asked for their verbal and written consent for their child to be included in the study and for their medical information to be used for research purposes. The carer information sheet and the consent form will be in English but will be also translated in Chichewa, the national language. The sheet will contain information on the study objectives, study procedures and anticipated duration of participation, potential risks and discomfort for the child, benefits for the child and for the under-five population in general, condition of study termination or participant withdrawal, confidentiality of records and contact persons in case any question or problem arise. When parents or carer withhold consent for participation, children will be referred to non-participating clinics providing the standard of care for SAM children. There are several such clinics in the selected Districts. They use standard P-RUTF. Any child who develops study food related side effects or any serious disease during the study will be referred to the appropriate level of care and the cost of the treatment met by the research project. Participating children and all SAM children will benefit from study. A committee of experts will be appointed to serve as the data monitoring and safety committee. They will be notified monthly of the trial's progress and of all the cases of study related side effects as they are diagnosed.

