#### 2.5.1.2 Efficacy trial

As stated in the hypotheses the main study will be a 3 group statistician blinded, randomized and controlled, parallel groups, **efficacy** non-inferiority trial. Because the participants will be able to distinguish the different RUTFs based on colour and mouth feel, participants will not be blinded. We will use the day care approach to ensure that children eat only the RUTF of the group to which they have been assigned. No study food will be taken home and the intake will be supervised by study enumerators who will in person feed the children.

The principal endpoints for the efficacy trial are:

1. Recovery rate
2. Mean weight gain
3. Mean time to recovery
4. Mean height gain
5. Percentage of body fat mass at recovery

6. Mean phase angle
7. Prevalence of anaemia
8. Incidence of deaths after discharge

The definition of principal endpoints is given below

(a) Recovery rate

The recovery rate will be measured as a percentage of those children who are discharged cured from the OTP programme divided by the total number of children who exit from the programme

$$\text{Recovery rate} = \frac{\text{No. children discharged Cured}}{\text{Total No. of Exit}} \times 100$$

(b) Average weight gain

The average weight gain will be measured as the mean of the growth velocity expressed in g/kg/day of individual children calculated as follow:

$$\text{Weight gain} = \frac{\text{Discharge weight (g)} - \text{Admission weight (g)}}{\text{Admission weight (kg)} \times \text{Length of stay (days)}}$$

$$\text{Average weight gain} = \frac{\Sigma \text{ weight gains}}{\text{Total children}}$$

(c) Average time to recovery or Length of stay

The average length of stay (LOS) is the mean of the LOS expressed in days of individual children calculated as follow:

$$\text{Average LOS} = \frac{\Sigma (\text{Discharge date} - \text{Admission date})}{\text{Total of children}}$$

(d) Average height gain

The average height gain is the mean of the height gain expressed in centimetres of individual children calculated as follow:

$$\text{Average height gain} = \frac{\Sigma (\text{Height 3 months after discharge (cm)} - \text{Admission height (cm)})}{\text{Total of children}}$$

(e) Prevalence of anaemia

The prevalence of anaemia will be expressed in percentage and calculated as follow

$$\% \text{ anaemia} = \frac{\text{n haemoglobin} < \frac{11.0\text{g}}{\text{dl}} * 100}{\text{total children with results}}$$

(f) Incidence of death after discharge

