†This CI is inconclusive in that it is still plausible that the true treatment difference is less than  $\Delta$ , but the new treatment is significantly worse than the standard.

From Piaggio et al, JAMA, 2006(295):1152-1160.

For the comparison of survival after discharge from the therapeutic feeding programme, the Kaplan-Meier method will be used to construct survival curves, and the log-rank test and a Cox-regression model will be used

to compare the survival of children who recovered from SAM to that of the community control and assess the effect of some socio-economical and clinical characteristics such as gender, age at discharge, nutrition status at admission and at discharge, HIV status, tuberculosis, and phase angle on survival. Interactions of all the outcomes with the variables gender, form of SAM (oedematous or non-oedematous) and HIV status will be checked.

Given that the study will recruit over a short period of 6 months, no interim analyses will be conducted. However, the independent data monitoring committee will have the right to request Interim analyses if there are reports of several cases of serious side effects.

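### Events reach the DMC by attribution, so an unattributed death or a by-arm excess of ordinary illness has no stated route to it

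*Protocol*

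**What the plan says.** Section 2.7 of the protocol gives the DMC a monthly notice of progress, with no stated content, and says that "all the cases of study related side effects will be reported to the DMC as they are diagnosed". It adds that "any side effects judged serious will be immediately reported by phone and email", with the DMC chair among the recipients. Section 1.7 repeats the routine rule: besides progress, the committee is notified "of all the cases of study related side effects as they are diagnosed".

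The committee's powers are wider than its feed. Under Section 2.7 the chair "will have the power to call for an extraordinary meeting in case of any report that is considered alarming", and may end the trial early on the committee's weighing of risk and benefit. On timing, "The DMC will meet at the beginning of the study and twice during the course of the study". One member is a statistician from outside the research team.

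Interim analysis appears twice. Section 1.5.4.2 says: "No interim analysis will be performed except if the monitoring and safety committee identify need for such analysis". Section 2.5.6.2.1 says that "the independent data monitoring committee will have the right to request Interim analyses if there are reports of several cases of serious side effects".

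On who sees the food, Section 2.5.1.2 says that participants can distinguish the products and are not blinded, and that "intake will be supervised by study enumerators who will in person feed the children". Only the analysing statistician is described as blinded.

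**The concern.** Reporting by attribution works when an event is rare and plainly linked to the product. Here the relevant harms resemble the background. The protocol cites a case fatality of 4.1% in community programmes (Section 2.1), warns of loose stools when RUTF is started (Section 2.8), and records fever, cough, diarrhoea and vomiting daily (Table 4). If a food caused more of these, no single child's episode need look like a side effect. The excess would show only when arms are compared.

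The people near the child, whose view would shape the judgement of relatedness, can know which food was given. That judgement can be coloured in either direction.

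At stake is whether the body with the power to stop the trial sees a between-arm difference while it can still act. The two study foods also differ from P-RUTF in iron, for which Section 2.1 itself records a concern about pathogenic gut bacteria.

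**Working it through.** The protocol states no iron dose per kg and no monitoring threshold, so there is no planned figure to reproduce. The check has three parts.

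**1. Routes to the DMC, side by side**

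| Route | Where | What opens it |
|---|---|---|
| Case reports as diagnosed | 1.7, 2.7 | Event called a study-related side effect |
| Urgent report | 2.7 | Event called a side effect and judged serious |
| Monthly notice | 1.7, 2.7 | None needed, but content unstated |
| Extraordinary meeting | 2.7 | A report considered alarming |
| Early stop | 2.7 | Committee's risk/benefit assessment |
| Interim analysis | 1.5.4.2 | Committee identifies a need |
| Interim analysis | 2.5.6.2.1 | Several serious side effects reported |

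The first two rows are filtered by attribution. The third could carry deaths but is not said to. The last four depend on what has already reached the committee. No row states that deaths, referrals or the daily illness record are sent whatever their cause, or that anything is tabulated by arm.

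**2. Iron dose by arm**

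Inputs: iron 60.0 mg (both study foods) and 12.0 mg (P-RUTF) per 100 g; energy 520.0 and 526.8 kcal per 100 g (Table 5); prescription 200 kcal/kg/day (Section 2.5.4.3.2).

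Formula: dose = (kcal/kg/day ÷ kcal per 100 g) × mg iron per 100 g.

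- Study foods: 200/520 × 60 = 23.1 mg/kg/day
- P-RUTF: 200/526.8 × 12 = 4.56 mg/kg/day
- Ratio: 23.08/4.56 = 5.1

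At the intakes reported from the DRC trial (Section 2.2), assuming the present products' densities:

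- Under 24 months: 152/520 × 60 = 17.5 against 167/526.8 × 12 = 3.8, ratio 4.6
- 24 months or more: 139/520 × 60 = 16.0 against 157/526.8 × 12 = 3.6, ratio 4.5

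**3. What coded-arm counts could show (illustration)**

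Planned size is 250 + 150 = 400 per arm (Table 2). Assume 200 per arm at an in-study meeting. For an excess p1 − p0, SE = √[p1(1−p1)/n1 + p0(1−p0)/n0].

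Deaths at the cited 4.1%: 0.041 × 200 = 8.2 expected, 16.4 if doubled.

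- One study food against P-RUTF: SE = √(0.082×0.918/200 + 0.041×0.959/200) = 0.024; 0.041/0.024 = 1.7 SE
- Both study foods against P-RUTF: SE = √(0.082×0.918/400 + 0.041×0.959/200) = 0.020; 2.1 SE
- With an assumed base risk of 2% to 5%, the doubling is 1.2 to 1.9 SE (one food) and 1.4 to 2.3 SE (both)

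Common illness, with assumed P-RUTF rates of 10% to 30% and an assumed 10-point excess: 2.8 down to 2.1 SE for one food, 3.4 down to 2.5 SE for both.

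Chance findings: six event types × two study foods × two meetings = 24 comparisons. If they were independent, the chance of at least one beyond 1.96 SE with no true effect is 1 − 0.95^24 = 0.71, and less if they are correlated. Such counts are signals for judgement, not tests.

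**The case against.** The strongest reply is that the committee is far from powerless. The monthly notice may well include deaths. The power to call a meeting covers any alarming report, with a serious food-related event given only as an example. The committee may ask for an interim analysis when it sees a need, and a risk/benefit stop presupposes more than isolated cases. Nothing withholds allocation from the DMC, and its statistician could count reported cases by arm. Table layouts and event lists commonly belong in a charter or SAP.

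Much of this stands. A reader might infer that the DMC is kept from seeing deaths or barred from by-arm data; the documents support neither. Nor is the absence of table shells a finding. What remains is narrower: the protocol itself writes the reporting rule, and writes it by attribution. A committee can count by arm only the cases it is sent.

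On iron, a reader might infer that the dose is hazardous. The documents do not support that. Section 2.8 reports DRC use at what reads as the same iron level without abdominal complaints, and Section 2.2 reports diarrhoea and vomiting there as consistent with acceptance equal to P-RUTF. Section 2.1 sets against the gut-bacteria concern the lack of a significant haemoglobin rise on P-RUTF and a Malawian study suggesting that iron is safe after severe malaria. The iron difference is a reason to compare arms, not evidence of harm.

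The two interim-analysis statements can be read together, since Section 2.5.6.2.1 does not exclude other grounds. But it is the detailed section, and it names only the narrower one.

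**Conclusion.** The point holds in limited form, as a cheap improvement. Sections 1.7 and 2.7 send events to the DMC by attribution. In a trial with distinguishable foods and an expected background of deaths and illness, an unattributed death or a by-arm excess of ordinary illness has no stated route to the committee. Partial routes exist through the unspecified monthly notice and the committee's general powers, so this is a badly set rule rather than an absence of oversight.

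The 5.1-fold difference in prescribed iron (about 4.5-fold at DRC intakes) follows from the protocol's own tables. The standard-error illustrations rest on assumed base rates, an assumed excess and an assumed 200 children per arm. They show that counts by arm would be informative but modest: a doubling of deaths from 4.1% is only 1.7 SE for one food.

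The text between Sections 2.8 and 2.10 was not available, so the statement that no route is given does not extend to it.

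**What to change.** - In Sections 1.7 and 2.7, state that all deaths, serious illnesses and inpatient referrals are reported to the DMC regardless of judged relatedness.
- In Section 2.7, state that at each of the two in-study meetings the DMC receives counts by coded arm of these events and of the daily-recorded diarrhoea, vomiting and fever. The DMC's independent statistician should handle them, and recovery data should be left out.
- In Section 2.5.6.2.1, word the interim-analysis trigger as in Section 1.5.4.2: the committee identifies a need.

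The cost is a short amendment, a little statistician time and two sets of tables, mostly from data already collected daily. Inpatient referrals have no row in Table 4 and would need one line on the card. The downside is chance imbalance across several event types and two looks, so the amendment should say that the DMC reads the counts as signals, not tests. No new visit or procedure is needed.
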